#### Impacts and Cost-Effectiveness of Rural Trial

Descriptive analyses of all baseline measures will include frequencies and valid percent for categorical variables, and mean, standard error, median, and interquartile ranges for continuous variables. Comparisons between the baseline and outcomes at short-, medium-, and long-term time points will be completed with parametric tests (eg, paired *t*-tests) or nonparametric test equivalents (eg, Mann-Whitney *U*) where appropriate. The primary outcome will be the Oswestry Disability Index. Multivariable regression analysis (as described by Salisbury et al [51]), conducted on an intention-to treat basis, will be used to investigate between-group differences in mean Oswestry Disability Index scores at the 6-month time point, with adjustment for baseline scores. The economic evaluation will be conducted using the cost utility analysis. This analysis will involve the use of the EQ-5D-5L health survey instrument [47], for which utility weights are available for a sample of the Canadian general population [52]. Multiple linear and logistic regression analyses will be used to determine the predictive models that best explain differences and changes in both outcomes and costs related to both productivity loss and health care costs.

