The objectives of this research study were to: (1) explore the *validity* (ie, diagnostic and management concordance) of an interprofessional assessment session with a PT and NP performed via secure videoconferencing, compared to a PT or NP in-person assessment alone; (2) examine the *impacts* and *cost-effectiveness* of an interprofessional assessment/education session with a PT and NP delivered via secure videoconferencing for people with CLBDs, compared to in-person PT only assessment/education session and usual care by an NP; and (3) explore the *perceived barriers and facilitators* of the use of secure videoconferencing for assessment and management of people with CLBDs living in rural underserved communities, from the perspectives of patients and health care providers.

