### Study Design and Data Collection

Concurrent to the intervention part of the study described below, 30 people with CLBDs were recruited from the Saskatoon, SK area. Each participant underwent an interprofessional assessment with an NP (in-person) and a PT (via videoconferencing), an in-person assessment with a second PT, and an in-person assessment with a second NP. Each PT and NP completed an online clinical classification tool, adapted from one previously developed by the author [39], to allow for an interrater comparison of diagnostic and management recommendation classification (ie, PT in-person vs NP in-person vs team of NP in-person with PT joining via secure videoconferencing).

The study design for Objectives 2 and 3 included two intervention groups and a control group, with 20 participants in each group: (1) interprofessional telehealth intervention; (2) in-person PT (travelling from Saskatoon, SK to provide services); and (3) *usual care* provided by an NP (see Figure 1). Due to the interprofessional nature of the intervention, the NP involved in the telehealth-based intervention group may have altered their *usual care* practice; therefore, the control group participants were drawn from the practices of 2 NPs that were not involved in the telehealth intervention, who provided services out of Carrot River. Participants were randomly assigned to 1 of the 3 groups using simple block randomization to ensure equal group sizes [40]. Participants allocated to either of the in-person PT group or the team telehealth intervention groups were eligible to receive up to 4 in-person PT treatment sessions delivered by an urban-based PT who travelled to the community (if recommended by the assessing health care providers).

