A combination of paper-based and online questionnaires measured outcomes at 4 time points, as shown in Figure 1: (1) *baseline*, prior to the health care encounter; (2) *short term*, within 2 weeks of the initial health care encounter; (3) *medium term*, 3 months postintake; and (4) *longer term*, 6 months postintake. Baseline questionnaires covered a range of sociodemographic (eg, age, gender, education, employment and other income, work status), clinical (eg, pain location, duration) and psychological (eg, fear avoidance beliefs, depression, somatization) factors. Phone or email reminders for completion of follow-up questionnaires were performed with phone or email prompts based on the tailored design method proposed by Dillman et al [41].

The multidimensional outcome measures have demonstrated reliability, validity, and responsiveness in similar clinical populations, and will cover the domains of back-specific function, general well-being/generic health status, pain, work disability, and satisfaction with care, as recommended by international groups of back pain researchers [42,43]. The primary outcome of interest will be self-perceived function, which was assessed using the modified Oswestry Disability Index, a back-specific self-report questionnaire [44,45]. The Numeric Pain Rating Scale [46] was used to measure the intensity of current pain, pain at its best, and pain at its worst levels over the last 24 hours. Quality of life/general health status was measured with the EuroQol health survey instrument (EQ-5D-5L) [47]. Patient satisfaction was measured using a modified version of the Visit-Specific Satisfaction Instrument, as described and validated by Kennedy et al [48], as well as a space for comments regarding satisfaction with the clinical encounter, as previously published [49]. Costs were captured using self-report diaries that recorded intervention/treatment costs, work status, absenteeism and disability days related to back pain, health service use within and outside of the study (ie, both government funded and nonfunded services), and other CLBD-related costs such as medication use (ie, prescription and nonprescription drugs) and travel time and costs from the beginning of the intervention period until the end of the study period (ie, 6 months postintake).

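### For pain and for earlier Oswestry scores, the only test the plan names is against baseline, not between the randomised arms, and its non-parametric example is not a paired test

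*Protocol article*

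**What the plan says.** Objective 2, at the end of the Introduction, is comparative: the impacts and cost-effectiveness of the team telehealth session are to be examined "compared to in-person PT only assessment/education session and usual care by an NP". Study Design and Data Collection describes a randomised three-arm trial: "Participants were randomly assigned to 1 of the 3 groups", "with 20 participants in each group". Outcomes are measured at baseline, within 2 weeks of the first encounter, and at 3 and 6 months.

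Impacts and Cost-Effectiveness of Rural Trial then sets out four pieces of analysis:

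- A general sentence on follow-up outcomes: "Comparisons between the baseline and outcomes at short-, medium-, and long-term time points will be completed with parametric tests", with the paired t-test as example, "or nonparametric test equivalents (eg, Mann-Whitney" U), where appropriate.
- For the primary outcome, an intention-to-treat multivariable regression for "between-group differences in mean Oswestry Disability Index scores at the 6-month time point, with adjustment for baseline scores".
- A cost-utility analysis that uses the EQ-5D-5L.
- Linear and logistic regressions, described as predictive models, to explain differences and changes in outcomes and costs. Arm is not named as a term.

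On satisfaction, Study Design and Data Collection says: "Patient satisfaction was measured using a modified version of the Visit-Specific Satisfaction Instrument". The same section places the baseline questionnaire before the health care encounter.

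**The concern.** A comparison of follow-up with baseline estimates change over time. In a randomised trial the effect of the care model is the difference between arms, and change within an arm is not that difference. The article's own definition of chronic low back disorder says that the condition is often episodic or recurrent, and some participants are recruited when they present for care. Some improvement is therefore to be expected in every arm, whatever the care model.

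Three things are at stake. Pain at all follow-ups and ODI at 2 weeks and 3 months could be reported in a form that does not answer Objective 2. A reader who sees a significant change in one arm and a non-significant change in another may take this as an arm difference, although that contrast has not been tested. And the trial is meant to supply effect sizes for a larger study, which will need between-arm estimates with their precision, not before-after p-values.

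**Working it through.** **What is named for each outcome**

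| Outcome | Test against baseline | Explicit between-arm contrast |
|---|---|---|
| ODI, 6 months | yes | yes, baseline-adjusted regression |
| ODI, 2 weeks and 3 months | yes | none |
| Pain, all follow-ups | yes | none |
| EQ-5D-5L, costs | EQ-5D-5L: yes, under the general sentence | through the cost-utility analysis, comparative by nature |
| Visit-specific satisfaction | probably not possible | none |

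The satisfaction row is an inference. The instrument rates a visit, and baseline precedes the encounter, so a score for that visit should not exist at baseline. The text gives no schedule of outcomes by visit, and the design figure is not shown.

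**How misleading separate before-after tests could be**

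The article gives no power figure for the rural trial, so there is nothing to reproduce. From the article: n = 20 per arm, 3 arms. Assumed, because not stated: two-sided 5% level, correlation ρ between baseline and follow-up of 0.5 to 0.7, and the same true change d (in SDs of the score) in every arm, so that no arm difference exists.

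1. SD of change = √(2(1−ρ)), which is 1.000 at ρ = 0.5 and 0.775 at ρ = 0.7.
2. Power p of one paired t-test comes from the noncentral t distribution with 19 degrees of freedom, noncentrality d√20 / SD of change, and critical value 2.093.
3. Chance that two arms differ in significance = 2p(1−p). Chance that three arms are not unanimous = 1 − p³ − (1−p)³.

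Example with d = 0.4 and ρ = 0.5: noncentrality = 0.4 × 4.472 / 1.000 = 1.789 and p = 0.397. Two arms: 2 × 0.397 × 0.603 = 0.479. Three arms: 1 − 0.063 − 0.219 = 0.718.

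| Common change d | p at ρ = 0.5, 0.6, 0.7 | Three arms not unanimous at ρ = 0.5, 0.6, 0.7 |
|---|---|---|
| 0.2 SD | 0.14, 0.16, 0.20 | 35%, 40%, 47% |
| 0.4 SD | 0.40, 0.48, 0.59 | 72%, 75%, 72% |
| 0.5 SD | 0.56, 0.66, 0.78 | 74%, 67%, 51% |
| 0.6 SD | 0.72, 0.81, 0.91 | 60%, 46%, 25% |
| 1.0 SD | 0.99, 1.00, 1.00 | 3%, 1%, 0% |

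For a single pair of arms, 2p(1−p) cannot exceed 50%, which it reaches at p = 0.5. In 20,000 simulated trials at ρ = 0.5, a direct t-test of change between two arms was significant in 4.9% to 5.1%. The like-for-like comparison is therefore up to 50% against about 5%.

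**The non-parametric example**

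Mann-Whitney U treats the two sets of scores as independent. In 4,000 simulations of 20 pairs at ρ = 0.5:

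| Test | Rejections, no change | Rejections, 0.5 SD change |
|---|---|---|
| Mann-Whitney U | 0.8% | 27% |
| Wilcoxon signed-rank | 5.1% | 54% |
| Paired t | 5.6% | 56% |

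Applied to paired data, Mann-Whitney U loses about half the power for the change it is meant to test.

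**Precision of the between-arm alternative**

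The difference detectable with 80% power at 20 per arm is (1.960 + 0.842) × √(2/20) = 0.89 SD of the analysed variable. Estimates with confidence intervals therefore suit these outcomes better than tests.

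**The case against.** The strongest reply is that the section does more than before-after testing. The primary outcome has a sound analysis: between-group, baseline-adjusted and by intention to treat. EQ-5D-5L and costs enter a cost-utility analysis, and Objective 2 makes that a comparison of care models. The closing regressions cover differences as well as changes, and nothing excludes arm from them. This stands as far as it goes. A reader might infer that every outcome except 6-month ODI is confined to tests against baseline, and the documents do not support that. However, models described as predictive, with no arm term named, neither confirm nor replace the contrasts for pain and earlier ODI.

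Second, the general sentence is loosely worded. It does not say that the tests are run arm by arm, nor that significant arms will be set against non-significant ones. Because Mann-Whitney U is an independent-samples test, some between-group use may have been intended. That is possible, but the sentence does not say so, and on either reading it needs correction.

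Third, the sentence is qualified by appropriateness and does not name satisfaction, so it need not cover an outcome without a baseline value. This is fair. A flat statement that the plan prescribes an impossible test for satisfaction would go too far.

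Fourth, secondary models may sit in a full protocol or SAP that is not shown, and the study calls itself predominantly a pilot. Silence would be no fault, but here the article names a method, and it is the method that does not fit. The pilot purpose argues for between-arm estimates, because those are what a larger trial would use.

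**Conclusion.** The point holds for pain at all follow-ups and for ODI at 2 weeks and 3 months: the only test explicitly named does not estimate the contrast that Objective 2 asks for. It also holds, without any assumption, that Mann-Whitney U is not the non-parametric counterpart of a paired t-test. For satisfaction the point is only probable.

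The percentages describe a risk that arises if readers infer arm effects from separate before-after results. They rest on the assumed level, correlation and common change. A reader might infer that a spurious arm difference is the most likely result. That is not established: the high figures belong to common changes of about 0.4 to 0.5 SD, the risk almost vanishes at 1.0 SD, and for one pair of arms it never exceeds 50%.

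The plan should be changed, but the 6-month ODI analysis is not affected.

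**What to change.** - Apply the baseline-adjusted, intention-to-treat between-arm regression already chosen for 6-month ODI to pain at each follow-up and to ODI at 2 weeks and 3 months. Report estimates with confidence intervals and label them secondary. One mixed model with arm-by-time terms is an option, not a requirement.
- Compare post-encounter satisfaction scores between arms without a baseline term.
- Report within-arm change descriptively, with confidence intervals.
- If a paired non-parametric test is kept, name Wilcoxon signed-rank in place of Mann-Whitney U. If a between-group test was meant, say so.

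Data collection is complete and analysis is in progress, so the cost is some wording and a little programming. The downside is that secondary estimates at 20 per arm will be imprecise, and the report should say so.

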#### Perceived Barriers and Facilitators for Videoconferencing

An inductive thematic analysis will be applied to qualitatively analyze the results of the semistructured interviews with the PTs and NPs involved in the team telehealth assessment, and a sample of patient participants from the team telehealth intervention arm. A process of open and axial coding will be applied. During open coding, a constant comparative approach will be used to group the codes into categories and identify themes. Axial coding will then be completed to look at the interrelationship of categories. A coding scheme will be developed jointly, and verified independently, by 2 researchers via identifying, classifying, and labeling the primary patterns in the data.

### Sample Size

A sample size of 30 for Objective 1 (validity) is adequate, based on an estimated minimum .60 kappa level between 2 PT raters and 80% power [50]. Determining the appropriate sample sizes to reach adequate power for Objectives 2 and 3 (rural community trial) is challenging, as there has been little comparable work in similar clinical populations from which to draw estimates of variance and effect sizes. Furthermore, the sample sizes suggested in the literature [46] far exceed what would was feasible given the budget, time lines, and caseload proportion of CLBDs in the rural community. A primary purpose of the intervention part of this study will be to estimate outcome variances and effect sizes, which could then be used to plan a larger, sufficiently powered, multi-site intervention.

### Ethical Considerations

The largest potential burden for participants was perhaps the amount of time required to complete the baseline and follow-up questionnaires (30-60 minutes). Some participants may have felt sensitive about recording psychosocial risk factors or health history; however, assurances of study data confidentiality and anonymity should have helped to address this. All study protocols complied with Health Information Protection Act standards. The VidyoDesktop platform is a private and secure means of sharing sensitive health and personal information between patients and health care providers. Consent forms were reviewed and signed by participants prior to starting the study. Study participants’ data will be confidential and identified only by study identification number; participants will not be identified in any reporting materials and only aggregate data will be presented during results dissemination. All data will be stored on a password-protected server at the University of Saskatchewan.

### Knowledge Translation

The proposed project will implement the Canadian Institutes of Health Research’s integrated knowledge translation approach, engage researchers and knowledge users throughout the research process, and maximize prospects for the use of findings in practice [53]. An array of clinical, community-based, and manager/decision maker knowledge users have been (and will continue to be) recruited to participate in this study, thereby shaping its design and driving health care practice implications. These partners will be consulted and engaged at key stages throughout the research process (ie, 1-2 times per year through a combination of in-person and teleconference/videoconference meetings over the course of the 3-year project).

## Results

This study was funded in July 2013 and the University of Saskatchewan Biomedical Research Ethics Board approved the study in November 2013. Participant recruitment began in September 2014 and data collection was completed in December 2015. Analyses are in progress, and results are anticipated in 2017. Results of the trial component of this study will comply with the CONSORT-EHEALTH checklist [54].

## Discussion

CLBDs are a widespread public health problem, particularly in rural and remote areas. New innovative models of care delivery are needed to address reduced access to PT services in many rural and remote communities worldwide. The aim of this project is to compare *usual care* delivered by a rural health care provider (ie, NP) with 2 means of integrating a PT into a rural primary health care setting: (1) PT joining via secure videoconferencing/telehealth for a team-based approach with the in-person NP; and (2) the PT travelling from an urban center to provide face-to-face services in a rural community. This study has the potential to inform rural and primary health care reform in Saskatchewan and beyond, to improve access to needed health services in underserved rural communities, and lead to the development of important partnerships that will lay the foundation of a Saskatchewan-based program of research. The lessons learned from this project regarding barriers and facilitators will help to inform effective strategies for implementation and evaluation of similar care models in different rural and remote communities and health care contexts. This research may also help to optimize management of a range of common chronic conditions in rural and remote settings.

Despite the novel contribution of this study to the literature, and its potential to inform health services reform and access, there are notable limitations. First, given the complex and heterogeneous nature of CLBDs and variability in the biopsychosocial experiences of those with CLBDs, the characteristics of participants in this study may not be reflective of the broader population with similar conditions. Second, the assessment and management of CLBD is similarly complex and heterogeneous. Although the primary aim of this study is the comparison of a team telehealth/videoconferencing approach to in-person PT or NP care, we anticipate wide intraprofessional (as well as interprofessional) variability in approaches, which may limit the replicability of the study intervention in other contexts and with different health care providers. Countering these limitations are the use of multidimensional outcome measures using both qualitative and quantitative approaches, which will allow for a more nuanced evaluation of the different care models. Unfortunately, this study does not include an in-person *team* approach (PT and NP) as one of the comparison groups. This omission is mainly due to scope limitations imposed by funding availability. Further research should examine the validity, feasibility, and impacts of this additional health delivery model for people with CLBDs. The current research is predominantly a pilot and feasibility study, but we anticipate that the findings and lessons learned from this study will nevertheless be valuable to inform future research and health services planning.

This study is the first step of a planned multi-stage research program in which future studies will investigate how similar interventions may work in different rural and remote communities, and with other types of chronic conditions and populations. The results of this project will lead to the development of evidence-informed approaches and community-based implementation strategies to improve access to PT services in primary health care settings in other rural and remote underserved areas, and potentially provide a framework for cost-effective and patient-centered models of service delivery for management of other chronic conditions. Furthermore, the partnership approach to health services research is crucial to lay the foundation for the development and evaluation of more extensive multi-site, community-informed, team-based interventions for people with CLBDs and other chronic health conditions living in rural and remote communities.

## Abbreviations

CLBD: chronic low back disorder
EQ-5D-5L: EuroQol health survey instrument
NP: nurse practitioner
PT: physical therapist
